### Study design

This study is a prospective multicenter clinical trial in The Netherlands. Patients with a macroscopic suspected and/or histological suspected T1 CC, meeting the in-and exclusion criteria, are eligible for inclusion. Based upon endoscopic images, the expert panel decide whether a lesion is suspect for a T1 CC. To reduce subjectivity and standardize the assessment, all expert panel members will use internationally applied scoring systems; Paris classification [25], Hiroshima classification [24] and report the morphological malignant features that are present. In particular the presence of a demarcated area with neoplastic pit pattern (Hiroshima C1-3) will weigh heavy when a lesion is screened for eligibility by the expert panel [26]. Depending on the macroscopic assessment and estimated depth of invasion, the expert panel will state if the lesion is suspected for T1 CC (superficial or deeply-invasive) and subsequently recommend which local resection strategie(s) (ESD, eFTR or CAL-WR) is/are suitable.

According to the recommendation of the current national Dutch colorectal carcinoma guideline, all suspected T1 CCs must be discussed in the local multidisciplinary team meeting to determine the best treatment strategy. If CAL-WR is regarded to be a suitable treatment by all parties, technically possible and preferred by the patient, inclusion of the patient will follow (Fig. 1). All eligible patients rejected for inclusion by the expert panel will be registered in a screening-log. Preoperative measurement of CEA (carcinoembryonic antigen) is required. In accordance with the current Dutch T1 CRC guideline, tumor staging through imaging of the chest and abdomen is not recommended in case of suspected T1 CRCs and therefore not indicated before the procedure. Written informed consent will be obtained and the patient and procedure related items will be registered in a web-based database (ResearchManager, Version 6.5). The estimated duration of inclusion will be 24 months and the total follow-up period of each patient is 5 year.

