### Histopathological examination

Over the last years, a nation-wide cohort of pathologists with special interest in gastro-intestinal oncology were extensively trained to score the above and below mentioned histological risk factors, in the context of the PATCH-study (https://t1crc.com/research—KWF Dutch Cancer Society reference number: 12723 / 2019–2). To guarantee a high-quality histopathological assessment, all the resected specimen will be judged by PATCH-trained dedicated pathologist(s) of the participating centers.

The specimen will be processed through the following instructions (standard care). The pathologist receives the fresh resected specimen in toto, without manipulation of the staple line by the surgeon. The pathologist removes the staples, the lateral margins and deep peritoneal aspect will be inked with different colors. Thereafter, the specimen will be stretched on a paraffin block (or mesh), photographed, and fixed for 24 h at room temperature. After fixation, longitudinal sections of limited length and width of the whole specimen will be included and the specimen will be accessioned in toto. Histological diagnosis of the tumor is carried out in accordance with the current guidelines and will include histological type, invasion depth, tumor grade, presence of vascular/lymph invasion, grade of budding and margin status. Incomplete resection is defined as a resection margin of less than 0.1 mm (R1) [29] and/or when radicality cannot be determined (Rx). T1 CCs with the presence of one or more histological risk factors, i.e. (lympho-) vascular invasion, poor (high-grade) differentiation (G3) and high-grade tumor budding (Bd2-Bd3), are classified as high-risk T1 CC.

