### Follow-up

After CAL-WR and subsequent histological examination, 3 groups will be formed i.e. (1) benign pathology, (2) low risk T1 CC (i.e. carcinomas with absence of histological high risk features for lymph node metastasis), and (3) high risk T1 CC (i.e. carcinomas with histological high risk features for lymph node metastasis) or accidentally found ≥ pT2 (Fig. 3). All patients diagnosed with a benign colonic polyp, will receive a follow-up colonoscopy after 1 year to evaluate local recurrence rate. Patients diagnosed with low risk T1 CC will undergo colonoscopy 12 and 48 months after curative radical (R0) resection, according to the current national guideline. In case patients are diagnosed with an incomplete resected low risk 1 CC, high risk T1 CC or ≥ pT2, completion surgery is advised. All patients with an indication for completion surgery will be staged with chest and abdomen imaging by computer tomography (CT) to rule out potential synchronous metastasis and will subsequently be discussed in the multidisciplinary team meeting. If completion surgery is considered to be beneficial, it needs to be performed within six weeks after initial CAL-WR in order to guarantee the patients’ oncological outcome [30]. In case of high complication risks and/or based on the patients’ choice, there can be refrained from a complementary resection and give preference to intensive follow-up. The impact of CAL-WR on QoL will be evaluated in all patients, also those that undergo completion surgery, using three questionnaires (EQ-5D-5L, QLQ CR29 and CWS). The questionnaires will be performed at baseline, at 3 and 36 months after the procedure. Participation in the national Prospectief Landelijk CRC cohort (PLCRC) is preferable for the questionnaires [31].

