#### Secondary endpoints

Effectiveness (technical success and macroscopic- and microscopic radical resection)30-day postoperative morbidity and mortality rate. Complications will be assessed according to the Clavien-Dindo classification. Clavien-Dindo grade I and II complications will be classified as minor and grade III-V complications as major.3-year metastasis free survival defined as the development of metastasis outside the area of the intended surgery (intensive surveillance), or after completion surgery.5-year overall survival and disease free survival (disease free survival is defined as the time between surgery until local cancer recurrence or detection of distant metastasis)Total procedure related and postoperative costs (‘in-hospital’ costs between the primary day of surgery until 30-days after discharge)Postoperative quality of life

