### Data analysis

Data on demographic and baseline characteristics will be summarized for continuous variables, in case of normal distribution by mean and standard deviation (SD), and in case of non-normal distribution by median and (interquartile) range. Discrete variables and categorical data will be presented as proportions of patients (percentages). All baseline characteristics and differences in secondary outcomes, such as morbidity and postoperative QoL, will be compared between patients that only received CAL-WR versus patients that received also additional oncologic resection, using the Student’s T-test (in case of normally-distributed continuous data) or the Mann–Whitney U test (in case of non-parametrical continuous data). Normality will be verified using the Kolmogorov–Smirnov test. A (two-sided) *p*-value < 0.05 will be considered significant. The primary endpoint will be described as the proportion (percentage with 95% confidence interval) of patients with pT1 CC where only local resection with CAL-WR appeared to be curative and thereby oncologic resection was prevented. The 5-year overall survival and disease free survival will be assessed using a Kaplan–Meier analysis*.* The 30-day postoperative morbidity and mortality will described as proportions (percentages). Data analysis will be performed by using the Statistical Program for the Social Sciences (SPSS) version 28.0 (IBM. Corp, Armonk, New York, USA).

The cost analysis will be conducted from a hospital’s perspective. Total procedure-related cost of CAL-WR will be calculated in Euro. Healthcare costs will be calculated by multiplying used healthcare services by the appropriated unit cost prices. Bottom-up micro costing will be applied. For all other healthcare services reference prices, will be used where available. Costs will be discounted to correct for inflation. Eventually, the cost efficiency of our strategy will be calculated, considering also the number of patients that will need two operations i.e. patients with high risk T1 or ≥ T2.

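### The cost analysis names discounting as the correction for inflation, and its definition of two-operation patients leaves out the incompletely resected low-risk T1 group that the Follow-up section also advises for completion surgery

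*Protocol article*

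**What the plan says.** All references are to the protocol article.

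- **Price adjustment (Data analysis).** Resource use is multiplied by unit prices, with bottom-up micro-costing and reference prices where they exist. Then: "Costs will be discounted to correct for inflation". The article gives no rate, index or price year.
- **Cost window (Secondary endpoints).** The endpoint covers in-hospital "costs between the primary day of surgery until 30-days after discharge".
- **Calendar period (Study design).** "The estimated duration of inclusion will be 24 months".
- **Two-operation patients (Data analysis).** Cost efficiency is to be calculated "considering also the number of patients that will need two operations i.e. patients with high risk T1 or ≥ T2".
- **Who is advised a second operation (Follow-up).** "In case patients are diagnosed with an incomplete resected low risk 1 CC, high risk T1 CC or ≥ pT2, completion surgery is advised". The Histopathological examination section treats a resection as incomplete if the margin is under 0.1 mm (R1) or if margin status cannot be established (Rx). The Background likewise gives incomplete resection as an indication for further surgery, alongside the histological risk factors.

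**The concern.** There are two separate defects in one paragraph.

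First, the named operation does not serve the stated purpose. Discounting weights costs by how long after a patient's starting point they fall, at a rate that expresses time preference. Inflation is a calendar-time matter and is handled by putting all unit prices on one price year. The sentence gives inflation as the reason for discounting, so an analyst who follows it would apply an adjustment with no real role in this window, and would still have no stated price year.

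Second, the two-operation group is introduced as a definition and names two indications where the Follow-up section names three. Patients with low-risk histology but an R1 or Rx margin are in the treatment pathway and absent from the cost definition. Leaving them out can only lower the count of second operations, so any error makes the strategy look cheaper. Costs belong to the study's stated aim and are a listed secondary endpoint, so the wording deserves to be right.

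**Working it through.** The plan states no cost figure, so there is none to reproduce. The first and third checks compare sections, and the second and fourth size the two effects.

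**1. Purpose against operation.** The cost window runs from surgery to 30 days after discharge. Every cost in it falls well within a year of the patient's start, so time preference has nothing material to act on. Price levels may still differ between calendar years during a 24-month inclusion period, but only if unit prices are taken from different years. The remedy for that is a common price year.

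**2. Size of discounting in this window.** The reduction is 1 − 1/(1 + r)^(d/365). The rates r are assumed, since the article gives none. I take d = 37 days (an assumed 7-day stay plus 30) and d = 72 days (the six weeks within which completion surgery is to be performed, 42 days, plus 30).

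| r per year | 37 days | 72 days |
|---|---|---|
| 3% | 0.30% | 0.58% |
| 4% | 0.40% | 0.77% |
| 5% | 0.49% | 0.96% |

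The range is about 0.3% to 1.0%, even with completion surgery inside the window.

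**3. Second-operation groups side by side.**

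| Group | Follow-up: completion surgery advised | Data analysis: counted as two operations |
|---|---|---|
| High-risk T1 | yes | yes |
| T2 and above | yes | yes |
| Low-risk T1, R1 or Rx | yes | no |

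The two sections disagree on the third row.

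**4. Illustrative size of the omitted row.** Inputs:
- 96 pT1 patients and 45% both low-risk and R0 (Sample size calculation). The 96 reproduces: 1.96² × 0.45 × 0.55 / 0.1² = 95.08, rounded up.
- R0 rates from earlier cohorts: 91% (Background, benign lesions) and 86% to 92% (Discussion, incompletely resected low-risk T1, n = 24).

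If margin status is independent of histological risk, the low-risk share is 0.45/R0 and the omitted group is 96 × (0.45/R0) × (1 − R0):
- R0 = 86%: 96 × 0.523 × 0.14 = 7.0
- R0 = 91%: 96 × 0.495 × 0.09 = 4.3
- R0 = 92%: 96 × 0.489 × 0.08 = 3.8

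That is about 4 to 7 patients.

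**The case against.** The best defence is that both sentences are loose wording with little consequence.

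On inflation, the stated purpose suggests that price adjustment was meant. Bringing later costs back to the first year's prices has the same algebraic form as discounting, with a price index in place of a discount rate. So one should not claim that the sentence necessarily pushes costs the wrong way. It still names the wrong operation and leaves the reader to guess which rate applies.

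A reader might also infer a large price distortion. With an assumed 3% to 10% yearly price change, prices would differ between the first and last patient by 6% (1.03² = 1.061) to 21% (1.10² = 1.21). The document does not support this. The rates are assumed, the contrast is the extreme one rather than the effect on mean cost, and there is no drift at all if one price list is applied to everyone's recorded resource use. The article does not say which prices apply.

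On second operations, the short definition mirrors the label of the third follow-up group. Elsewhere in Data analysis, the comparison group is patients who also received an additional oncologic resection, whatever the reason, which would include R1/Rx reoperations. The undercount is therefore a risk if the definition is followed literally, not a certainty. The contradiction between the sections remains.

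A reader might go further and say that 5% to 10% of planned second operations are lost, by setting 4 to 7 against about 72 (96 × 0.55 = 52.8, plus 143 × 0.90 × 0.15 = 19.3). The article plans no such number. It requires everyone advised surgery to have it, whereas the Follow-up section allows surgery to be withheld for complication risk or patient choice.

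Finally, price-year detail is often left to a fuller document. That excuses the missing index and year, but not a sentence that states the wrong method or a definition that conflicts with another section.

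**Conclusion.** Both defects stand, at minor severity. Discounting is the wrong correction for inflation and changes costs by only about 0.3% to 1.0% in this window, at assumed rates of 3% to 5%. The definition of two-operation patients contradicts the Follow-up section by omitting R1/Rx low-risk T1. If applied as written, it would understate second operations and favour the strategy.

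The omitted group of about 4 to 7 in 96 is an illustration only. It rests on R0 rates borrowed from benign lesions and from a small cohort of 24, on independence of margin status and histological risk, and on the planned 45%. It counts patients advised completion surgery, not patients who undergo it. The effect is confined to a secondary cost outcome.

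**What to change.** Replace the discounting sentence with: *Unit costs are expressed in one stated reference price year, using a price index where source prices come from other years; no discounting is applied because the cost horizon is under one year.* The choice of index can stay with the investigators. Discounting would become relevant only if costs beyond one year were brought in.

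Reconcile Data analysis with Follow-up by counting, in the cost-efficiency calculation, every patient who actually has completion surgery, including those with R1/Rx low-risk T1. Counting operations performed also deals with patients who decline or are spared surgery, and takes no position on who should have it.

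The cost is two sentences, with no change to recruitment, sample size or the primary analysis. The only downside is that the estimated cost of the strategy may come out slightly less favourable.

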### Ethics

The study protocol is approved by the Medical Ethics Committee of the Isala clinics, Zwolle (NL81497.075.22). The study will be conducted according to the rules on medical research involving human subjects (Medical Research (Human Subjects) Act), in Dutch: Wet Medisch Wetenschappelijk Onderzoek met mensen (WMO) and the principles of the Declaration of Helsinki (64th WMA General Assembly, Fortaleza, October 2013).

## Discussion

The substantially rising incidence of stage I CRC emphasizes the urgent need for a more widely applicable local resection technique in order to prevent unnecessary major oncologic surgery. This prospective multicenter study aims to give insight in the effectiveness, safety, and costs of CAL-WR as local resection technique for T1C CCs. Furthermore, patients will be followed for a total duration of five years, allowing us to evaluate the short and long-term oncological outcome of CAL-WR as primary resection strategy.

The biggest challenge in this study is to include patients with T1 CC as accurately as possible. Identification of malignant morphologic features such as depression, excavation and spontaneous bleeding, combined with evaluation of the vascular pattern using the Hiroshima Classification, is currently used in standard clinical practice to differentiate between adenomas and T1 CCs. In a large multicenter study in the Netherlands, Backes et al. achieved a sensitivity of 78.7% with a specificity of 94.2% using this standardized assessment [27]. Optical discrimination between deep submucosal invasive T1 and T2 CC is also challenging. To minimize the inclusion of benign or ≥ T2 lesions, we implemented an expert panel of five dedicated gastroenterologist to reassess all eligible patients. In order to reduce inter-observer variation, each independent member of the expert panel, as well as the referring gastroenterologist, will estimate the chance of T1 malignancy using international scoring systems with low-threshold use of the risk stratification developed by Backes et al. [27]. Moreover, our expert panel will be trained to macroscopically differentiate between deep submucosal invasive CCs and ≥ T2 CCs by using a scoring system composed of five endoscopic findings which was developed by Koyama et al. [28]. These 5 endoscopic findings (deep depression, demarcated depressed area, fold convergency, erosion or white plaque, and Borrmann type 2 or 3 tumor) combined in a scoring system resulted in a sensitivity and specificity of respectively 82% and 83% in their development cohort. Despite the precautions taken in this study protocol to limit inclusion of adenomas and ≥ T2 colon carcinomas, it shall be unavoidable to include purely T1 CCs. This margin is taken into account in our sample size calculation.

In contrast to earlier insights, deep submucosal invasion (T1b) is not considered as independent risk factor for lymph node metastasis [18]. In the absence of other histological risk features (i.e. poorly differentiation, high grade tumor budding, (lympho-)vascular invasion), patients with deep submucosal invasive T1 colon carcinomas have no longer an indication for major oncologic surgery. Therefore, deep submucosal invasion was not included as criterion to advice an additional oncologic resection after radical CAL-WR in this protocol. Prior endoscopic resection or attempt is in this study handled as exclusion criterion to guarantee an unbiased sample population. However, outside study context CAL-WR is also suited to perform scar excisions of irradical endoscopically removed low-risk pT1 colon carcinoma. In the recent prospective clinical trial by Leicher et al. [22, 32], a technical success rate of 90% was achieved with R0 resection rates variating from 86%-92% for irradical resected low-risk T1 colon carcinomas, however numbers were small (*n* = 24).

In the study of Leicher et al., macroscopic recurrent tissue was found during follow up colonoscopy in four cases of which three cases were initial radical (R0) resections. The indication to perform CAL-WR in these patients were either a difficult location of the polyp or a non-lifting polyp. In all these patients, initial and recurrence histology was benign. Considering this recurrence rate, all patients with definite benign histology in this study, will receive a follow-up colonoscopy 1 year after CAL-WR, regardless of current surveillance guidelines.

A significant part of patients with suspected T1 CC are not eligible for removal by eFTR due to the size of the lesion. Expertise with ESD in the proximal colon is often not available in non-academic hospitals. Moreover, ESD leads more often to an incomplete resection in case of deep submucosal invasion [19]. Our hypotheses is that CAL-WR will safely expand the local therapeutic armamentarium that is currently available for T1 colon carcinomas. In particular for deep-invasive CCs, CAL-WR could fill in the gap between endoscopic minimally invasive local resection techniques and major oncologic surgery, preventing unnecessary major oncologic surgery.

## Data Availability

The datasets generated and/or analyzed during this study are not publicly available due to individual privacy but are available from the corresponding author on reasonable request.

## Abbreviations

CAL-WR: Colonoscopy-Assisted Laparoscopic Wedge Resection
CC: Colon carcinoma
CEA: Carcinombryonic antigen
CRC: Colorectal cancer
eFTR: Endoscopic Full Thickness Resection
ESD: Endoscopic Submucosal Dissection
LNM: Lymph-node metastases
PLCRC: Prospective Dutch Colorectal Cancer (PLCRC) cohort
QoL: Quality of Life
